#### **12.1.4.2 Cohort Review Meetings:**

**Ad-hoc meetings can be called at any moment if needed for Safety consideration (DSMB).**

The dose-escalation process will be monitored by a **cohort review committee (DSMB, see corresponding chapter 8.2.2. for the dose escalation rules)**.

A cohort review meeting will be organized once all patients at a specific dose level have completed the V1 to V3 DLT period to decide regarding dose escalation. A cohort review meeting will also be organized as soon as DLTs are observed in 2 or more patients to decide about stopping the dose escalation and confirming the Maximum Tolerated Dose (MTD) has been reached:

Cohort1: 3 first patients in this cohort will allow the assessment of a potential unexpected safety signal and will confirm feasibility of the procedure. The CRC will review patients after treatment completion of the 3 patients. Safety, tolerability and DLT events between V1 and V2 will be evaluated to take the decision on dose escalation.

Cohorts 2&3: These cohorts present a more classical posology (daily treatment of 1 and 3 capsules respectively) in the microbiome capsule category (see section introduction). The CRC will review patient tolerability after treatment completion of the 6 patients of the evaluated cohort, completed with follow up information from of the previous cohorts. Tolerability and DLT events between V1 and V3 will be evaluated to take the decision on dose escalation.

Cohorts 4&5: No more dose regimen escalation are expected. Tolerability of those patients will of course be closely monitored. Because cohort4 will first be completed, a SC will validate the step up to cohort5.

The focus of this meeting will be to review the overall patients' safety and to ensure all DLTs have been identified to decide escalation to the next dose level, or to confirm if the MTD has been reached.

At the time of the decision to escalate the dose, the cohort review committee may recommend one or more of the following with the aim of establishing an MTD and/or enhancing potential safety and tolerability:

- That additional medication is used
- That specific measures are taken in the treatment of side effects based on AEs and building upon the cumulated experience in their management
- That caution is exercised in patients presenting with conditions that may exacerbate any observed toxicities

The cohort review committee may permit enrollment of additional patients in any cohort to ensure that there is the required number of patients with evaluable DLTs at each dose level cohort.

The cohort review committee may review and delay enrollment into the next dose cohort based on observed toxicities.

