- **1st level of dose for 1st cohort:** - 3 Patients will be treated with one capsule/day on day 1 and D7. The Safety Committee (SC) will evaluate occurrence of Limiting Toxicity after the 3 patients will have completed V3. If no patient experiments a DLT, the following cohort will use dose level 2 *i.e.* 1 capsule/Day for 7 days. If one or more patient experiment a DLT, the SC might consider study stop recommendation or cohort continuation. The purpose of this cohort is to assess feasibility of the whole procedure and check any unexpected tolerability issue that would prohibit continuation of the experimentation. As the dose schedule is not considered as sufficient enough to allow for any effective activity, it will not be considered for the choice of final dose.
- **2nd Level of dose (cohort2):** 6 patients will be treated with 1 capsule/day for 7 days. The Safety Committee (SC) will evaluate occurrence of Limiting Toxicity after the 6 patients will have completed V3. If no or 1 patient experiments a DLT, the following cohort will use dose level 3 *i.e.* 3 capsules/day for 7 days. If two or more patients out of 6 experiment a DLT, the study will be stopped.
- **3rd level of dose (cohort3):** 6 patients will be treated with 3 capsules/day for 7 days. The Safety Committee (SC) will evaluate occurrence of Limiting Toxicity after the 6 patients will have completed V3. If no or 1 patient experiments a DLT, the following cohort will use dose level 4 *i.e.* 3 capsules/D for 14 days and dose level 5 *i.e.* 9 capsules/day for 7 days. If two or more patients out of 6 experiment a DLT, the study will be stopped.
- **4th level of dose:** 6 patients will be treated with 3 capsules/day for 14 days. The Safety Committee (SC) will evaluate occurrence of Limiting Toxicity after the 6 patients will have completed V3. If no or 1 patient experiments a DLT, the following cohort will use dose level 5 *i.e.* 9 capsules/day for 7 days. If two or more patients out of 6 experiment a DLT, the study will be stopped. Of note, if 2 or more DLT are reported during the 7 first days of treatment, then the SC will re-assess cohort3 evaluation.

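### Section 12.1.4.2 bases the first escalation on DLTs up to V2, while section 8.2.2 and the DLT window run to V3

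*Protocol*

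**What the plan says.** Section 8.2.2 sets the cohort 1 schedule ("3 Patients will be treated with one capsule/day on day 1 and D7") and the time of review: "The Safety Committee (SC) will evaluate occurrence of Limiting Toxicity after the 3 patients will have completed V3". It then gives the rule. With no DLT: "If no patient experiments a DLT, the following cohort will use dose level 2". With one or more: "If one or more patient experiment a DLT, the SC might consider study stop recommendation or cohort continuation".

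Sections 8.3.1 (primary endpoint) and 12.1.4.1 (tolerability) both run the DLT window from V1 to V3. Section 12.1.4.2 opens in the same way, with a cohort review meeting "once all patients at a specific dose level have completed the V1 to V3 DLT period to decide regarding dose escalation", and refers to 8.2.2 for the escalation rules.

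The cohort 1 paragraph of 12.1.4.2 then departs from this:

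- Timing: "The CRC will review patients after treatment completion of the 3 patients".
- Window: "Safety, tolerability and DLT events between V1 and V2 will be evaluated to take the decision on dose escalation".

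The paragraph for cohorts 2 and 3 names the V1–V3 window but keeps the looser timing: "The CRC will review patient tolerability after treatment completion of the 6 patients of the evaluated cohort".

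**The concern.** The first escalation gate has two written rules. One counts DLTs to V3, the other only to V2. The cohorts 2 and 3 paragraph uses the same sentence form with V3, so a reader can take V2 as a deliberate exception for cohort 1 and not as a slip.

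V2 is a poor place to stop counting. Cohort 1 exists to pick up unexpected tolerability problems, yet V2 is scheduled around the day of the second capsule. The named window therefore holds almost no observation after the last dose and can close before it. A DLT that appears after V2 in one of 3 patients moves the cohort out of automatic escalation under 8.2.2 and does not count under the cohort 1 sentence of 12.1.4.2. The next cohort would then start on an incomplete reading of the first.

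**Working it through.** The protocol gives no figure that depends on this point, so there is nothing to reproduce. The check is a comparison of the text plus day arithmetic.

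**Which window each place uses for cohort 1**

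| Protocol section | Window or review time |
|---|---|
| 8.2.2, first dose level | review after V3 |
| 8.3.1, primary endpoint | V1 to V3 |
| 12.1.4.1, DLT follow-up | V1 to V3 |
| 12.1.4.2, opening rule | V1 to V3 |
| 12.1.4.2, cohort 1 paragraph | V1 to V2, review after treatment completion |

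**Inputs**

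- Capsules on D1 and D7 (8.2.2).
- V2 on D7, allowed D5 to D9 (11.1.5).
- V3 on D19, allowed D14 to D24 (11.1.6).

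**Observation after the second capsule** (visit day minus 7)

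- V2: 5 − 7 = −2 to 9 − 7 = +2 days; nominal 7 − 7 = 0.
- V3: 14 − 7 = 7 to 24 − 7 = 17 days; nominal 19 − 7 = 12.
- Of the 5 allowed V2 days, 2 (D5, D6) precede the capsule and 1 (D7) coincides with it.

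**Share of the DLT window left out by stopping at V2** (elapsed days from D1, so V2 = 6, range 4 to 8; V3 = 18, range 13 to 23)

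- Nominal: (18 − 6)/18 = 12/18 = 67%.
- Least (V2 on D9, V3 on D14): (13 − 8)/13 = 5/13 = 38%.
- Most (V2 on D5, V3 on D24): (23 − 4)/23 = 19/23 = 83%.

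**Effect on the decision**

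Under 8.2.2, 0 DLTs in 3 patients leads to dose level 2, and 1 or more opens a discussion of stopping the study or continuing the cohort. A single DLT after V2 is therefore enough to make the two rules disagree.

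**What follows the gate**

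Level 2 treats 6 patients with up to 7 capsules each, against 2 capsules each at level 1: 7/2 = 3.5 times the total. The amount on a dosing day stays at 1 capsule, so the step is in frequency.

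**Whether another rule catches the late DLT**

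- The mandatory early meeting in 12.1.4.2 needs DLTs in 2 or more patients.
- The suspension rule at the end of 8.2.2 covers cohorts 2 to 5 only and also needs 2 patients.
- Section 12.1.4 has the committee evaluate tolerability once per cohort, so no second cohort 1 review is guaranteed.
- The cohorts 2 and 3 review includes follow-up from earlier cohorts, but only after the 6 patients at the next level have been treated.

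**The case against.** The best reply is that the governing rule can be identified. Section 12.1.4.2 points to 8.2.2, opens with the V1–V3 period and asks the meeting to make sure that all DLTs are known. One sentence stands against several. This makes V3 the likely intent, but the sentence at fault is the one written specifically for cohort 1, and nothing marks it as an error.

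A second reply is that a late DLT is not lost. AEs are recorded to V4, SAEs are entered within 24 hours, ad hoc meetings can be called at any time, and the committee may delay the next cohort. Section 8.2.2 also requires no particular action after one DLT; it only removes automatic escalation. These points reduce the harm. They depend on someone choosing to act, whereas the V1–V3 rule counts the event without that.

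Third, treatment completion is only a lower bound on review timing, and V3 satisfies it. That is fair. The outright contradiction is the V1–V2 phrase, and the timing wording, including that for cohorts 2 and 3, needs clarifying only because it permits an early review.

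Finally, the percentages are shares of calendar time, not of risk, and V3 may follow standard of care, so its bounds are less firm than they look. Both points stand.

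**Conclusion.** The concern holds: the cohort 1 sentence in 12.1.4.2 is wrong as written. It conflicts with 8.2.2, 8.3.1, 12.1.4.1 and the opening rule of its own section. Followed literally, it omits nominally two thirds of the DLT window and gives at most 2 days of observation after the last capsule.

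The day counts rest on the stated visit windows and on the second capsule being taken on D7. No probability of wrongful escalation is given, because the protocol states neither a DLT rate nor when DLTs would occur.

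The weight is moderate. The defect affects one gate in a 3-patient feasibility cohort that 8.2.2 excludes from the choice of final dose, and under 8.2.2 every later level has its own review after V3. It should still be fixed, because it is a safety gate and the correction is almost free.

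**What to change.** In section 12.1.4.2:

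- Cohort 1 paragraph: hold the review once the 3 patients have completed V3, and evaluate DLTs from V1 to V3.
- Cohorts 2 and 3 paragraph: hold the review once the 6 patients have completed V3. The window is already right.

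As minor harmonisation only, replace the 7-day follow-up in 12.1.4.3 with completion of the V1–V3 DLT period.

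If cohort 1 has already been reviewed, the sponsor should record which window the committee applied.

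The cost is amendment wording. The cohort 1 review comes nominally 19 − 7 = 12 days later than under the V2 reading. The range is 14 − 9 = 5 to 24 − 7 = 17 days, since the review cannot precede the D7 capsule. This is no later than 8.2.2 already requires, and no visits or patients are added.

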#### **12.1.4.3 Recommended Phase 2 Dose RP2D**

Once the MTD or MED is determined, or once the highest dose has been reached without declaring an MTD, the cohort review committee will select the recommended dose for the following studies with MaaT033 (recommended Phase 2 dose; RP2D).

RP2D usually is the highest dose with a pre - specified DLT rate. In this study, this dose will be the MTD, a dose below the MTD, or any other dose suggested upon clinical evaluation or all available safety, activity and efficacy parameters.

In case an RP2D is selected that is not the MTD, a minimum of 6 patients will need to be treated and followed-up for 7 days at this dose level (with a maximum of 1 DLT observed), before declaring it as the RP2D.

|                                                                                   |                    |                                                                      |
|-----------------------------------------------------------------------------------|--------------------|----------------------------------------------------------------------|
| [figure not shown] | DOCUMENT    | Protocol ID : MPOH05
EudraCT N° : 2019-004253-89
Version: 10.0 |
|                                                                                   | CIMON STUDY | Date : 04 MAY 2021
Page 50 / 70                                   |

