#### 11.1.6 New cycle START, Visit 3 - D19 (D14-D24)

This visit will be performed as Standard of Care or at day 19 (+/-5days).

During this visit:

- The physician will proceed to a physical exam including collection of vital signs and clinical evaluation
- Blood samples (30mL) and fecal swabs will be collected (See Table 1 for analysis details)
- Evaluation of treatment tolerability, acceptability, compliance and safety
- Urine or serum pregnancy test will be performed

Nasopharyngeal (or any other validated methods: salivary test, oro-pharyngeal test or other) and fecal SARS-CoV-2 tests will be performed.

During this visit, the patient will report to the physician any adverse reaction or severe event occurred since the previous visit.

All AE and SAE must be reported in the eCRF.

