#### **12.1.4.1 Tolerability consideration:**

Investigators will be trained regarding the mode of action of the investigational medicinal product and to be particularly attentive to any signs of toxicity.

**Dose Limiting Toxicity (DLT):** Based on the literature and our preclinical data, no particular toxicity is expected. Toxicity events will be defined as any at least possibly related adverse event grade  $\geq 3$  based on CTCAE v5.0 criteria. Due to the specific therapeutic protocol that blood cancer patients usually follow, the follow-up of patients in term of DLT is set from V1 (end of neutropenia) to V3 (start of a new chemotherapy cycle, or consolidation). Nevertheless, there are some anatomical or physiological system events that will be considered as expected in the context of patients with AML or HR-MSD, and thus not related to the treatment. Such events will only be considered DLT when grade  $> 3$ :

- Blood and lymphatic system disorders (DLT when grade 4 or 5)
- Immune system disorders (DLT when grade 4 or 5)

Depending on the number of DLTs, the dose is either escalated (0 DLTs) or de-escalated ( $\geq 2$  DLTs). Due to our specific drug activity assessment goals, cohorts 2 to 5 will systematically be expanded with 3 extra patients (0 or 1 DLTs) each.

|                                                                                   |                    |                                                                      |
|-----------------------------------------------------------------------------------|--------------------|----------------------------------------------------------------------|
| [figure not shown] | DOCUMENT    | Protocol ID : MPOH05
EudraCT N° : 2019-004253-89
Version: 10.0 |
|                                                                                   | CIMON STUDY | Date : 04 MAY 2021
Page 49 / 70                                   |

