## 14.2 ANALYSIS POPULATIONS

- Screened patients: all patients having signed an informed consent form
- Enrolled patients: all patients having been enrolled at V1
- Intent to treat (ITT) population: enrolled patients
- Treated patients: all enrolled patients having undergone at least one capsule intake (safety set)
- Per protocol (PP) population: all patients belonging to the ITT population with at least 60% of treatment and completion of V1, V2 and V3, with no major protocol violations (PP set)

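### The 7-day follow-up rule for an RP2D that is not the MTD (12.1.4.3) contradicts the V1–V3 DLT period; planned levels 2 to 5 are not affected

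*Protocol*

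**What the plan says.** Section 12.1.4.3 governs how the RP2D is chosen. It leaves the choice wide: "this dose will be the MTD, a dose below the MTD, or any other dose suggested upon clinical evaluation", together with the available safety, activity and efficacy data. If the chosen dose is not the MTD, "a minimum of 6 patients will need to be treated and followed-up for 7 days at this dose level", with no more than one DLT.

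The other sections that deal with DLTs use a longer period:

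- Section 12.1.4.1: "the follow-up of patients in term of DLT is set from V1 (end of neutropenia) to V3", the start of the next chemotherapy cycle.
- Section 12.1.4.2: "A cohort review meeting will be organized once all patients at a specific dose level have completed the V1 to V3 DLT period".
- Section 8.2.2, for each of levels 2 to 5: the Safety Committee "will evaluate occurrence of Limiting Toxicity after the 6 patients will have completed V3", and the level passes with zero or one patient with a DLT.
- Section 8.3.1: the primary endpoint runs from visit 1 to visit 3.

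Section 11.1.6 places V3 at day 19 with a window of 5 days either side. Day 7 is V2, the interim visit (section 11.1.5). The one shorter review is that of cohort 1, which 12.1.4.2 assesses on V1 to V2. That cohort has three patients, and 8.2.2 rules it out as the final dose.

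**The concern.** The same criterion, at most one DLT in six patients, appears with two different minimum observation periods. The shorter one sits in the section that fixes the dose for the following studies. Taken literally, it would let six patients support an RP2D at the time of the interim visit, before the DLT period used for every eligible planned level has closed. For the 14-day schedule it would also be satisfied halfway through treatment, although 8.2.2 says that tolerability may depend on duration. What is at stake is whether an RP2D outside the planned levels could rest on less safety follow-up than the protocol asks of the planned ones. This is not a detail that can wait for a statistical analysis plan, because the protocol itself sets the rule.

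**Working it through.** **Inputs.** RP2D rule: 6 patients, 7 days, at most 1 DLT (12.1.4.3). DLT period: V1 to V3 (8.2.2, 8.3.1, 12.1.4.1, 12.1.4.2). V3: day 19 ± 5 (11.1.6). Level 4: 3 capsules a day for 14 days (8.2.2). Maximum sample size: 27 (9.3).

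**The protocol's own figures.** 19 − 5 = 14 and 19 + 5 = 24, which reproduces D14–D24. 3 + 4 × 6 = 27, so the five cohorts use every planned patient.

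**Share of the DLT period covered by 7 days.**

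| V3 on | Share observed | Days not observed |
|---|---|---|
| D14 | 7/14 = 50% | 7 |
| D19 | 7/19 = 37% | 12 |
| D24 | 7/24 = 29% | 17 |

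For the 14-day course, 7 × 3 = 21 of 14 × 3 = 42 capsules, or 50%.

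**The other reading.** The phrase could mean treated, and then followed for a further 7 days. A 7-day course then reaches 7 + 7 = about D14, the earliest edge of the V3 window, so the mismatch remains whenever V3 is later. A 14-day course reaches 14 + 7 = about D21, which falls short only if V3 is after D21.

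**Which doses are exposed.**

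- Level 1 cannot be the final dose (8.2.2).
- Levels 2 to 5 each have six patients assessed after V3 (8.2.2), so their evidence already exceeds the 7-day minimum.
- A dose or duration outside these levels, which 12.1.4.3 allows, has no cohort or review of its own in the plan, and none of the 27 places is free for it.

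**Illustration of size.** The protocol states no DLT rate or timing, so both are assumed. Let p be the true DLT risk over V1–V3, with constant hazard and V3 at day W.

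- Risk seen by day t: q = 1 − (1 − p)^(t/W).
- Chance that 6 patients show at most 1 DLT: pass(x) = (1 − x)^6 + 6x(1 − x)^5.
- Chance of passing at day t but failing by V3: pass(q) − pass(p).

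For t = 7 and W = 19:

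| p | q by day 7 | pass at day 7 | pass at V3 | Difference |
|---|---|---|---|---|
| 2% | 0.7% | 0.9992 | 0.9943 | 0.5 points |
| 5% | 1.9% | 0.9950 | 0.9672 | 2.8 points |
| 10% | 3.8% | 0.9804 | 0.8857 | 9.5 points |

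Sensitivity at p = 2%, 5% and 10%:

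- V3 at D14: 0.4, 2.4 and 8.0 points. V3 at D24: 0.5, 3.0 and 10.2 points.
- Hazard halved after day 7, V3 at D19 (day-7 share 7/13): 0.4, 2.2 and 7.5 points.
- Seven days after a 7-day course (t = 14), V3 at D19: 0.3, 1.4 and 4.6 points.
- Seven days after a 14-day course (t = 21): zero for V3 up to D21; 0.1, 0.7 and 2.3 points at D24.

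**The case against.** The strongest reply is that the sentence decides almost nothing. Every dose level eligible under the plan is already judged at V3. Six patients at any other dose would exceed the 27 places and would probably need an amendment, which could set its own review rule. Section 12.1.4.1 also fixes the DLT follow-up of patients in general terms, and 7 days is stated as a minimum. Nor is a declaration at day 7 likely in practice. Section 12.1.4.3 opens RP2D selection only once the MTD or minimum effective dose is determined or the highest dose is reached. The RP2D is to rest on engraftment (7.2), and Table 4 places the sample analyses at the end of the study.

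Most of this stands, and it limits the point to a low-severity correction. It does not reconcile the two periods, and an amendment that added a dose would inherit the 7-day standard unless the sentence is changed.

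Three stronger readings are tempting but unsupported:

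- A reader might infer that patients added later escape the V3 review, because "The cohort review committee may permit enrollment of additional patients in any cohort". The rest of that sentence ties the additions to reaching the required number with evaluable DLTs in the cohort, and 12.1.4.2 reviews the cohort after V3.
- A reader might cite the per-protocol set (14.2), which requires V3. That defines an analysis population and is not an RP2D criterion.
- A reader might extend the calculation to DLT risks of 20% to 50%, where the differences are much larger. Nothing in the protocol supports such risks. Section 12.1.4.1 expects no particular toxicity, and section 6.4 reports 1 related serious event in 81 patients, although with other formulations.

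Even at 2% to 10%, the difference is not a clear measure of harm. Those risks lie below the tolerated one in six (17%), so passing such a dose may be the right decision.

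**Conclusion.** Wrong as written, low severity. The 7 days in 12.1.4.3 conflict with the V1–V3 DLT period that the protocol applies to the same limit in six-patient cohorts, and cover 29% to 50% of it. This follows from the text and the visit windows and needs no assumption. The reading of 7 days after the course narrows the conflict but does not remove it.

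The practical effect on levels 2 to 5 is nil. A reader might conclude that a planned level could be declared the RP2D on 7 days of data. Section 8.2.2 excludes this, because six patients must complete V3 at each of those levels. The conflict has effect only if the committee uses the option of another dose, probably after an amendment. For that case the illustrative size is about 0.5 to 9.5 percentage points. It rests on an assumed DLT risk of 2% to 10%, a constant hazard, V3 at D19 and the literal reading.

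**What to change.** In 12.1.4.3, replace the phrase on 7 days of treatment and follow-up, with its DLT limit, by: *treated at this dose regimen and followed from V1 to V3 (with a maximum of 1 DLT observed over that period)*. Add that a patient who has a DLT counts towards the limit whatever number of capsules was taken.

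Do not add a 60% compliance condition here. Section 9.3 already has that rule for replacing patients. Repeated in the RP2D rule, it could drop from the count a patient who stopped early because of a DLT.

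The cost is one sentence of text, with no added patients, visits or follow-up for levels 2 to 5. For an unplanned dose only, declaration would wait about 12 more days per patient with V3 at D19 (7 at D14, 17 at D24).
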